### Data and statistical analysis

Results will be included in the final analysis from patients who have complied with correct intake of study medicine. Patients, who fail to do so, will be excluded. Patients, who die during the study period, will be included in a survival analysis. Patients who must discontinue study medication due to a serious adverse event (SAE) will be followed closely until their condition is resolved and relevant treatment is completed. SAEs will be reported to the local health authorities.

Interim analysis will be conducted when 100 TEG-hypercoagulable patients have been enrolled and undergone three-month MSCT.

For categorical variables, χ^2^ tests or Fisher’s exact test will be used as appropriate. For continuous variables, analysis will be performed with the two-sample t-test, after ensuring normal distribution of the data. Data with no normal distribution will be analyzed with the Wilcoxon’s rank-sum test. *P*-values below 0.05 will be statistically significant. Multivariate analyses will be performed, including both demographic and procedural confounding factors. Survival analysis will include a Kaplan-Meyer plot.

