### Description of medical intervention

Aspirin 75 mg is restarted within 24 hours of surgery, in accordance with the current recommendations from ECS/EACTS
[13]. In the intervention group clopidogrel is started at Day 2 after surgery, with a 300 mg oral bolus to achieve greater initial platelet inhibition
[24,25]. Thereafter, clopidogrel therapy is continued with a daily dose of 75 mg for 90 days. Our study is the first study in CABG patients to utilize initial oral bolus of 300 mg clopidogrel. Greater loading doses of clopidogrel (that is, 600 mg) were not utilized due to bleeding concerns - in particular GI bleeding - in the postoperative setting, expressed by the cardiac surgeons at our institution.

Patients will receive study medication (clopidogrel) from the study nurse for the whole study period. At three months the patients are requested to bring in their remaining medication, so compliance can be assessed.

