### Limitations

Due to lack of funding no placebo drug is used, and this is why the open label design was chosen. However, we find it plausible to assume that the primary endpoint of graft patency after three months will not be affected by the lack of placebo drug in the control group, as the MSCT evaluators are blinded.

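### The final analysis keeps only patients who complied with study medicine, and the one compliance check described can apply only to the clopidogrel arm, so patients can be removed from one arm after randomisation

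*Protocol article*

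**What the plan says.** Under Data and statistical analysis, the Protocol article fixes the analysis set: "Results will be included in the final analysis from patients who have complied with correct intake of study medicine". It continues: "Patients, who fail to do so, will be excluded". No intention-to-treat or other all-randomised analysis appears anywhere in the article, and no numerical compliance threshold is given.

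Description of medical intervention identifies the study medication: "Patients will receive study medication (clopidogrel) from the study nurse for the whole study period". It then gives the compliance check: "At three months the patients are requested to bring in their remaining medication, so compliance can be assessed". Under Design and randomization procedure, controls receive aspirin only.

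Two further groups are mentioned under Data and statistical analysis. For deaths: "Patients, who die during the study period, will be included in a survival analysis". Patients who stop study medication because of a serious adverse event (SAE) "will be followed closely until their condition is resolved and relevant treatment is completed". Neither sentence says how these patients enter the patency comparison.

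Limitations defends the open-label design by arguing that, because the scan readers are blinded, "the primary endpoint of graft patency after three months will not be affected by the lack of placebo drug in the control group".

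**The concern.** The primary outcome under Outcome measures is worded in terms of patients assigned to dual therapy. An analysis restricted to compliers does not estimate the effect of that assignment, because it compares groups selected by what happened after randomisation.

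The selection is also unlikely to act equally. The check works on returned clopidogrel, so it can find non-compliers in the intervention arm and has nothing to count in the control arm. Timing adds to this. Patients are randomised the day before surgery, but clopidogrel starts on Day 2 after it. Read literally, an intervention patient with a difficult early course who never starts the drug is excluded, while a comparable control stays in. The Background names thrombosis as the main cause of vein graft occlusion in exactly this early period. It also reports more bleeding on dual therapy in other populations, so some stopping of clopidogrel is foreseeable.

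The rule refers to the final analysis as a whole, not to patency alone. A patient who stops clopidogrel because of a stroke or infarction could therefore be lost from the thromboembolic comparison as well.

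**Working it through.** **1. The plan's own figure.** Inputs from Sample size: patency 80% and 90%, 80% power, 5% significance. With two-sided z values of 1.96 and 0.8416:

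n = [1.96·√(2×0.85×0.15) + 0.8416·√(0.80×0.20 + 0.90×0.10)]² / 0.10² = 199 grafts per group.

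With the continuity correction that approximates Fisher's exact test, n = (199/4)·[1 + √(1 + 4/(199×0.10))]² = 219. This matches the plan. Exact Fisher power at 219 grafts per group is 81.2%. Then 219/2 rounds up to 110 patients, and the planned 125 allows for 15/125 = 12% drop-out. No stated figure is in dispute. All calculations here treat grafts as independent, as the plan does.

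**2. Size of the possible bias (illustration).** Assume no drug effect, true patency of 80% in both arms, 250 grafts randomised per arm, and exclusions in the clopidogrel arm only. Let d be the fraction excluded and q the patency among those excluded. Patency in the remaining clopidogrel patients is (0.80 − d·q)/(1 − d).

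- d = 12%, q = 70%: (0.80 − 0.084)/0.88 = 81.4%, a gain of 1.4 points.
- d = 12%, q = 60%: (0.80 − 0.072)/0.88 = 82.7%, a gain of 2.7 points.
- d = 12%, q = 90%: (0.80 − 0.108)/0.88 = 78.6%, a loss of 1.4 points.

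The table gives the spurious gain and, in brackets, how often a nominal two-sided 5% test rejects (normal approximation).

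| Excluded | q = 80% | q = 70% | q = 60% | q = 50% |
|---|---|---|---|---|
| 12% | 0 (5.0%) | 1.4 (6.6%) | 2.7 (11.7%) | 4.1 (20.8%) |
| 20% | 0 (5.0%) | 2.5 (10.2%) | 5.0 (27.8%) | 7.5 (56.6%) |

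The documents give neither d nor q. The 12% borrows the plan's drop-out allowance, which the plan applies to both groups and does not equate with non-compliance.

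**3. Power when all randomised patients are analysed.** Assume non-compliers in the clopidogrel arm have control patency (80%). Intervention patency becomes 0.90(1 − d) + 0.80d. Power is for Fisher's exact test with 250 grafts per arm, that is, with all 125 patients scanned.

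| Non-compliance | Intervention patency | Grafts needed per group | Patients per group | Power with 125 per group |
|---|---|---|---|---|
| 0% | 90.0% | 219 | 110 | 86.3% |
| 5% | 89.5% | 245 | 123 | 81.9% |
| 10% | 89.0% | 275 | 138 | 76.7% |
| 12% | 88.8% | 288 | 144 | 74.5% |

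Power falls below 80% between 5% and 10% non-compliance.

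**The case against.** Several stronger readings are tempting, and the text does not carry them.

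- **Compliance is measured in one arm only.** This is an inference. The article does not say that aspirin intake is ignored in controls, and Multiplate testing, including the agonist for aspirin effect, is scheduled without restriction to one arm. It is presented as monitoring of platelet reactivity, however, and not as a criterion for entering the analysis. What stands is that the only compliance check described can apply only to clopidogrel.
- **Patients who stop for an SAE are not scanned.** The article does not say this. It plans the three-month scan without exception for them. It leaves open whether they count as non-compliant, although the exclusion rule read literally would catch them.
- **Deaths are confined to a survival analysis.** The text says they are included in one, not that they appear nowhere else, and cardiovascular death is also part of a secondary outcome. A patient who dies before three months has no scan under any analysis set. This is a missing-outcome question, secondary to the exclusion rule.
- **The bias favours clopidogrel.** That rests on assumed low patency in those excluded. The Discussion links hypercoagulability to more graft occlusion and to low bleeding risk. On that reasoning, patients who stop for bleeding might have equal or better patency, which gives no bias or the opposite bias.

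The Limitations sentence concerns the missing placebo rather than the analysis set, so its bearing here is indirect. Still, blinded reading protects how a scan is read, not which scans are analysed. An unseen analysis plan does not answer the main point either, because the exclusion is stated outright and not left open.

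**Conclusion.** The point holds. As written, the final analysis is restricted to compliers, there is no all-randomised analysis, and the described check can remove patients from the intervention arm only. Allocation is still randomised, but the groups compared would not be. This needs correcting before the final analysis, because the rule can by itself create, inflate or hide a difference in the primary outcome.

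The size cannot be known from the documents. Under the assumed 12% exclusion with 60–70% patency, the spurious gain is 14–27% of the 10-point target, and the false-positive rate rises from 5% to 6.6–11.7%. There is no bias if excluded patients have the same patency as the rest, and it reverses if theirs is better. A reader should not infer a proven bias towards clopidogrel, nor that discontinuers go unscanned.

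**What to change.** - Replace the complier rule under Data and statistical analysis: the primary analysis includes all randomised patients in the arm assigned, whatever their tablet intake. Apply the same set to the secondary comparison of events between arms.
- State that the three-month scan already planned is sought in all survivors, including those who stopped clopidogrel, and give the analysis status of patients who stop because of an SAE.
- Prespecify sensitivity analyses for deaths and missing scans, for example one counting grafts of patients who die of cardiovascular causes as occluded and one using multiple imputation.
- Keep the complier analysis as secondary, with one definition of compliance that can be applied in both arms.
- Add to Limitations that reader blinding does not address exclusions made after randomisation.

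**Cost.** The wording change is small, but the effect estimate will be somewhat diluted. The stated 80% power should be rechecked and restated against an explicit non-compliance assumption. With 125 per arm it holds at 5% non-compliance and not at 10% under the assumption used above. Trial status reports 135 patients already randomised, so any scans missed in patients now past three months cannot be recovered and must be handled as missing.

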### Sample size

All patients receive a pedicled left internal thoracic artery graft at our institution; therefore, every patient on average will receive an additional two SVGs. Graft patency for SVGs is approximately 90% after one year. Under the assumption that TEG-Hypercoagulable patients have a lower SVG patency of 80%, and that dual antiplatelet therapy will raise the graft patency of these patients to the rate in uncomplicated patients (90%), calculations based on the Fischer exact test with 80% power and 5% significance level, show the following:

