#### ***Improvement of graft patency from 80% to 90%: 219 grafts per group***

With an average of 2 SVGs per patient; 219/2 = 110 patients in each group.

We will include 125 patients in each group to account for “drop-outs” and be able to detect at a significance level of 5% or better.

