## Trial status

Currently 135 patients are randomized in this trial, and inclusion is ongoing.

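### The interim analysis on primary-endpoint scans is not reconciled with the single P<0.05 rule: comparing patency between arms at both looks would take the false-positive rate to about 6% to 9%, above the stated 5%

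*Protocol article*

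**What the plan says.** Under *Data and statistical analysis*, the protocol article plans one interim look: "Interim analysis will be conducted when 100 TEG-hypercoagulable patients have been enrolled and undergone three-month MSCT". *Outcome measures* makes graft patency on MSCT at three months the primary endpoint, so the trigger is that endpoint being available in 100 patients.

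The same section names chi-square or Fisher's exact test for categorical variables and then gives its only threshold: P-"values below 0.05 will be statistically significant". It makes no distinction between interim and final analysis.

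*Sample size* rests on "calculations based on the Fischer exact test with 80% power and 5% significance level". The result is 219 grafts per group, or 110 patients, raised to 125 per group for drop-outs so as to "be able to detect at a significance level of 5% or better". Nothing is set aside for an earlier look.

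*Trial status* adds: "Currently 135 patients are randomized in this trial".

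**The concern.** Three statements stand side by side: a look at primary-endpoint data in 100 patients, one blanket threshold of 0.05, and a claim that the trial works at 5% or better. If patency is compared between arms at the interim and again at the end, each time at 0.05, a true null has two chances to be declared significant, and the claimed level no longer holds.

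At stake is the error rate of the primary conclusion. The look comes at 100 of 250 patients, when the estimate is still imprecise. With about 100 grafts per arm, Fisher's exact test has only about 44% power for 80% versus 90% patency. A nominally significant interim difference would therefore tend to be an exaggerated one. Treatment is open-label and the trial is run at one institution. The scan readers are blinded, which protects the patency readings but not the significance level.

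**Working it through.** **Inputs from the protocol article**
- Interim: 100 patients with three-month MSCT (*Data and statistical analysis*).
- Final: 250 randomised; 220 is the number needed before the drop-out allowance (*Sample size*).
- Patency 80% versus 90%, 5% level, 80% power, two vein grafts per patient (*Sample size*).
- Threshold 0.05, chi-square or Fisher (*Data and statistical analysis*).

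**Step 1. Reproduce the plan's own figure.** Two-sided 5% (z = 1.960), 80% power (z = 0.842), mean proportion 0.85:

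n = [1.960·√(2·0.85·0.15) + 0.842·√(0.8·0.2 + 0.9·0.1)]² / 0.10² = 198.96, so 199.

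With continuity correction: n' = (n/4)·[1 + √(1 + 4/(n·0.10))]² = 218.5, so 219.

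This matches the stated 219 grafts per group. Exact Fisher power at 219 per group is 81.2%. One-sided versions give 157, or 177 with correction, and do not match. The plan's 5% is therefore a two-sided 5% for a single analysis.

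**Step 2. Error rate with two looks at 0.05.** Let Z1 and Z2 be the interim and final statistics, bivariate normal under the null with correlation √t, where t is the information fraction.

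Overall error = 1 − P(|Z1| < 1.96 and |Z2| < 1.96).

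| Information at interim | Overall error |
|---|---|
| 100/250 = 0.40 | 8.63% |
| 100/220 = 0.455 | 8.46% |
| 0.50 | 8.31% |

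The result hardly depends on how many patients are evaluable at the end.

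**Step 3. Check with the tests the plan names.** Simulation under the null used 400,000 runs with independent grafts, 100 per arm (50 patients × 2) and then 250 per arm (125 × 2).

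| Test | Common patency | Final look alone | Either look |
|---|---|---|---|
| Chi-square | 80% | 5.0% | 8.7% |
| Chi-square | 85% | 5.0% | 8.7% |
| Chi-square | 90% | 4.9% | 8.7% |
| Fisher | 80% | 3.9% | 6.3% |
| Fisher | 85% | 3.8% | 6.2% |
| Fisher | 90% | 3.6% | 5.7% |

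Fisher's exact test is conservative, so its inflation starts from below 5%, yet the second look still takes it above 5%.

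**Step 4. Levels that restore 5% at t = 0.40.**
- P<0.001 at the interim with 0.05 at the end: 5.04%.
- P<0.001 at the interim with 0.0496 at the end: 5.00%.
- O'Brien-Fleming-type spending of a two-sided 5%: 0.0019, then 0.0492; overall 5.00%.

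**Step 5. Cost in power.** A final test with 80% power at 0.05 has drift 1.960 + 0.842 = 2.802. At 0.0496 the critical value is 1.963 and power is Φ(2.802 − 1.963) = 79.9%. At 0.0492 it is 1.967 and power is Φ(2.802 − 1.967) = 79.8%.

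**The case against.** The strongest reply is that the article announces an interim analysis, not a comparison of arms. It names no endpoint to be tested, no option to stop and no claim to be made. A blinded, pooled, safety or futility look would not raise the false-positive rate in this way, and sizing the trial at the full 5% is consistent with such a look. The purpose and boundary of an interim are also details that an article may leave to the full protocol or analysis plan, neither of which is shown.

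Much of this stands. A reader might infer that the trial will test patency twice at 5%, or that it may stop early for benefit. The text supports neither as fact, and the absence of a boundary elsewhere is not shown. What remains is narrower: the article itself publishes a blanket 0.05 rule next to an interim triggered by primary-endpoint data, and claims 5% or better. Taken literally, that rule allows a significant result at either look, and nothing in the article excludes it. This is a rule stated too broadly, not just an omitted detail.

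It is also fair to object that 8.6% should not be quoted alone. The trial was sized on Fisher's exact test, for which the figure is about 6%. A reader might further want to combine the interim with the correlation of grafts within patients to reach a larger figure. The article gives no design effect, and clustering is a separate question, so no combined figure is supported.

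**Conclusion.** The point holds conditionally. If the arms are compared on patency at both looks and P<0.05 at either counts as significant, the overall false-positive rate is about 8.6% with chi-square (8.5% at 100/220) and about 6% with Fisher's exact test. Both exceed the level the article claims.

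The figures assume a two-sided test, equal allocation, independent grafts and an information fraction of 0.40 to 0.455. They do not apply if the interim carries no efficacy comparison. Because the article does not say which kind of look is meant, its threshold and its interim need to be reconciled before the final data are seen.

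**What to change.** 1. Limit the P<0.05 rule to the final analysis, subject to point 3, and state the purpose of the interim.
2. If efficacy is not tested at the interim, say that no efficacy claim and no stopping for benefit can follow from it. The final test then keeps 0.05.
3. If efficacy is tested, declare it only at P<0.001 (Haybittle-Peto), with the final test at about 0.0496, for an overall 5.0%. O'Brien-Fleming-type spending is an alternative. State its convention: spending a two-sided 5% gives an interim level of about 0.0019, and spending a one-sided 2.5% gives about 0.0008.
4. With 135 patients already randomised, record whether the look has taken place and, if so, that no efficacy claim was made from it. If one was made, it has to be disclosed and reflected in the final level.

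The cost is a few sentences and, under point 3, a power loss of about 0.1 to 0.2 percentage points.

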**Conclusions:**

The present trial is the first randomized clinical trial to evaluate whether TEG-Hypercoagulable CABG patients will benefit from intensified antiplatelet therapy after surgery. Monitoring of platelet inhibition from instituted antithrombotic therapy will elucidate platelet resistance patterns after CABG surgery. The results could be helpful in redefining how clinicians can evaluate patients preoperatively for their postoperative thromboembolic risk and tailor individualized postoperative antiplatelet therapy.

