### High on-treatment platelet reactivity and thromboembolic risk

In recent years, there has been a growing acknowledgement of the association between insufficient platelet inhibition from instituted antiplatelet therapy (that is, clopidogrel and/or aspirin) and thromboembolic complications. Studies in PCI patients have demonstrated a significantly higher risk for post-procedure thromboembolic episodes in individuals that demonstrate high on-treatment platelet reactivity to ADP
[3,20-22]. Few studies have demonstrated that after conventional CABG with cardio-pulmonary bypass up to 50% of the patients will be transiently aspirin resistant, and this high on-treatment platelet reactivity has been correlated to early SVG thrombosis after CABG
[3,23]. The platelet reactivity patterns of clopidogrel after cardiopulmonary bypass have not been examined. We will monitor platelet reactivity in our trial to elucidate the patterns and degree of high on-treatment platelet reactivity of aspirin and clopidogrel in the immediate postoperative period and three months after CABG.

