**Figure 1 F1:**
[figure not shown]
Study flow chart.

The study nurse, utilizing the sealed envelope technique, randomizes 250 TEG-Hypercoagulable (TEG MA >69 mm) patients on the day before CABG, allocating 125 patients to the interventional group (receiving clopidogrel for three months and lifelong aspirin) and 125 TEG-Hypercoagulable patients to a control group (receiving lifelong aspirin only).

TEG, Multiplate aggregometry and routine blood samples are obtained the day before surgery, on Day 4 after CABG, and at three months postoperatively.

MSCT is conducted at three months after surgery.

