### Outcome measures

Primary:

Graft patency assessed at three months by MSCT will be significantly improved in TEG-Hypercoagulable patients allocated to dual antiplatelet therapy with clopidogrel and aspirin as compared to aspirin alone.

Secondary:

1. TEG-Hypercoagulable patients will suffer fewer thromboembolic events (that is, MI, stroke, pulmonary embolism, gastrointestinal ischemia, deep vein thrombosis) or cardiovascular death when on clopidogrel and aspirin vs. aspirin alone.

2. Assess if the degree of surgically induced hypercoagulability itself is an independent factor of graft occlusion, thromboembolic events and death.

3. High on-treatment platelet reactivity in spite of Aspirin and/or clopidogrel treatment, as evaluated by Multiplate aggregometry, increases the risk of thromboembolic events after CABG surgery.

All outcome measures will be evaluated at three months postoperatively.

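### The analysis section names only independent-sample tests and makes no exception for TEG and Multiplate, which are measured three times in the same patients (minor)

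*Protocol article*

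**What the plan says.** Data and statistical analysis assigns tests by type of variable. For continuous data: "For continuous variables, analysis will be performed with the two-sample t-test, after ensuring normal distribution of the data". Where normality fails: "Data with no normal distribution will be analyzed with the Wilcoxon’s rank-sum test". For categorical data, chi-square "tests or Fisher’s exact test will be used as appropriate". No exception is made for variables measured repeatedly, and no paired or repeated-measures method is named. The section adds: "Multivariate analyses will be performed, including both demographic and procedural confounding factors". The pre-operative value of a marker is not among the factors listed.

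Design and randomization procedure gives the sampling schedule: "TEG, Multiplate aggregometry and routine blood samples are obtained the day before surgery, on Day 4 after CABG, and at three months postoperatively".

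Two places state an interest in how the markers behave after surgery. The Background section on high on-treatment platelet reactivity says the trial will monitor the patterns and degree of "high on-treatment platelet reactivity of aspirin and clopidogrel in the immediate postoperative period and three months after CABG". The Abstract's Conclusions say: "Monitoring of platelet inhibition from instituted antithrombotic therapy will elucidate platelet resistance patterns after CABG surgery". In Outcome measures, TEG and Multiplate appear as predictors. Secondary outcome 2 reads: "Assess if the degree of surgically induced hypercoagulability itself is an independent factor of graft occlusion, thromboembolic events and death". Secondary outcome 3 relates Multiplate reactivity to thromboembolic events.

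**The concern.** The main continuous measurements that the article describes are serial, while the tests it names are for unrelated groups. Two uses of the markers are affected differently.

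**Change over time.** The Background cites aspirin resistance that is transient after bypass. Whether resistance fades is a question about the same patient on Day 4 and at three months. A two-sample test of those two sets of values ignores the pairing. With positive within-patient correlation the standard error is then too large, and a real change could be reported as not significant.

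**Comparison between arms.** The title includes assessing the antithrombotic effect of the two regimens. An unadjusted comparison of Multiplate at one time point makes no use of a pre-operative value that the schedule already provides.

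**Working it through.** **The plan's own figure.** None is stated for any TEG or Multiplate comparison. The only sample-size figure is for graft patency, 80% against 90%, with 80% power at the 5% level. The usual two-sided formula for two proportions gives (1.960·√(2·0.85·0.15) + 0.842·√(0.8·0.2 + 0.9·0.1))² / 0.1² ≈ 199. The continuity correction, (199/4)·(1 + √(1 + 4/(199·0.1)))², gives 219 grafts per group, as stated. Then 219/2 = 109.5, rounded to 110 patients, and 110/(1 − 0.12) = 125. This reproduces and does not bear on the point.

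**Inputs for the markers.** The schedule and the tests are as quoted. The documents give no standard deviation and no within-patient correlation ρ, so ρ is an assumption, shown at 0.3, 0.5 and 0.7 with equal variances at the two times. Results are normal approximations and do not depend on n, except the detectable differences in step 3.

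**1. Two-sample test applied to two time points in n patients.**
- True SE of the mean change: SD·√(2(1 − ρ)/n). SE used by the two-sample test: SD·√(2/n). Ratio: 1/√(1 − ρ).
- True size of a nominal 5% test: 2·(1 − Φ(1.960/√(1 − ρ))).
- Power where a paired test has 80%: Φ(2.802 − 1.960/√(1 − ρ)), with 2.802 = 1.960 + 0.842.

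| ρ | SE ratio | True size | Power (paired test 80%) |
|---|---|---|---|
| 0.3 | 1.20 | 1.9% | 68% |
| 0.5 | 1.41 | 0.6% | 51% |
| 0.7 | 1.83 | 0.03% | 22% |

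Simulation with 125 patients and 20,000 trials gave true sizes of 1.93%, 0.58% and 0.03%.

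**2. Two-sample test between arms at one time point.** The same simulation, with 125 per arm, gave a size of 4.99%, 4.97% and 4.96%. The test keeps its level.

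**3. Gain from adjusting the arm comparison for the pre-operative value.** The variance of the adjusted difference is 1 − ρ² times the unadjusted one. With 125 per arm, the smallest difference detectable with 80% power is 2.802·√(2/125) = 0.354 SD unadjusted, and 0.354·√(1 − ρ²) adjusted.

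| ρ | Variance cut | Detectable difference | Power (unadjusted 80%) |
|---|---|---|---|
| 0.3 | 9% | 0.338 SD | 84% |
| 0.5 | 25% | 0.307 SD | 90% |
| 0.7 | 49% | 0.253 SD | 97.5% |

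**4. Smaller gain for TEG maximum amplitude (MA).** Randomization requires MA above 69 mm, and the Background reports 87/200 = 43.5% of CABG patients above that cut-off. Assuming normality, keeping only the upper 43.5% leaves v = 0.329 of the baseline variance. The correlation among those randomized becomes ρ√v / √(ρ²v + 1 − ρ²), so 0.3, 0.5 and 0.7 fall to about 0.18, 0.31 and 0.49. The variance cuts shrink to about 3%, 10% and 24%.

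**The case against.** The strongest reply is that the article plans no test of one time point against another. Outcome measures lists no change-over-time hypothesis, and the statements on reactivity patterns are descriptive. Two-sample tests are named in a trial with two randomized groups, so the natural reading is that they compare those groups. This stands: a reader might infer that the plan's time comparisons carry a wrong standard error, but the documents support this only conditionally, if the rule is carried over to the stated aim.

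A reader might also infer that the arm comparisons are invalid or throw the pre-operative value away. Neither is supported. The unadjusted test keeps its level (step 2). Secondary outcome 2 depends on the rise from the pre-operative TEG value. Per-patient change could be compared between arms by a two-sample test, which is valid, although its variance relative to the unadjusted comparison is 2(1 − ρ) = 1.4, 1.0 and 0.6 at the three correlations, against 0.91, 0.75 and 0.51 with adjustment. Multivariate analyses are also planned, and nothing bars a baseline marker from them.

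The assumed correlations may be generous. Perioperative anticoagulation says aspirin and clopidogrel are routinely stopped five days before surgery, so the pre-operative Multiplate value is largely off-treatment while the later ones are on-treatment. The Multiplate section also says kaolin TEG cannot show the effects of these drugs, so the case for adjusting arm comparisons rests mainly on Multiplate.

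Last, a condensed article may leave models for serial laboratory data to the full protocol or analysis plan. That would answer a complaint about silence. Here the article does state a rule for all continuous and categorical variables, and the rule does not fit its serial markers.

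**Conclusion.** The point holds as a minor one. The stated rule covers the serial markers and does not suit them. Used for change over time, it would be conservative, with the loss of size and power shown in step 1; it would not produce excess false positives. Used between arms at one time point, it is valid and costs only precision, by the amounts in step 3 for Multiplate and step 4 for MA. All of these magnitudes rest on assumed correlations, since the documents give none. The graft patency outcome and its sample size are unaffected.

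**What to change.** In Data and statistical analysis, keep the named tests for comparisons between groups of variables measured once, and add two sentences for TEG and Multiplate:

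- **Change over time:** paired t-test or Wilcoxon signed-rank test for continuous values and McNemar's test for high-reactivity status, or a mixed model across the time points.
- **Comparison between arms:** ANCOVA, or a mixed model over Day 4 and three months, adjusted for the same marker's pre-operative value.

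The cost is wording and slightly more analysis work, with no new samples, visits or patients. Patients lacking one of two samples drop out of the simple paired tests; a mixed model can keep them. Trial status reports 135 patients randomized and inclusion ongoing, so the methods can still be fixed before the final analysis.
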